### Data collection, management, and protection

Data will be collected by a specialized research assistant, who will be responsible for the patient consents and case report forms. Soft copies of the research materials will be saved on a storage device not connected to the Internet. All data will be maintained in a locked storage and only those with permission from the PI will be able to access the data. All the retained data will be coded to identify the patients instead of personal information.

The IRB will oversee the intra-study data sharing process, with input from the Data Management Subcommittee. The PIs will be given access to the cleaned datasets. In order to ensure confidentiality, the project team members will be blinded to any identifying participant information.

### Monitoring

To ensure that the quality of the data are in accordance with the predetermined protocol and SOPs, the regular day-to-day monitoring will be carried out by a qualified clinical research investigator specified by the Scientific Research Department of Baoshan Hospital of Integrated Traditional Chinese Medicine and Western Medicine, Shanghai. The investigator will be blinded to the allocation and will examine whether the recruitment procedures and data recording followed the protocol in the case report forms. The investigator will discuss the unpredictable changes in the research process, such as changes to the eligibility criteria, treatment regimens, or duration of follow-up with independent researchers and statisticians. In the case of SAEs or crucial issues, the investigator will determine whether the events are acceptable or whether it is necessary to change or terminate the trial.

Thus, the investigator will oversee the compliance of the study protocol and informed consent documents, supervise the trial progress, participant recruitment, data quality, timeliness, the performance of the interventions, and all fields and process of the trial. If any important protocol modifications or violations arise during the trial, they will be handled by an independent researcher, who is responsible for preparing an amended protocol and resubmission to the IRB for a final decision under the direction of the IRB.

### Ethics and dissemination

The study was planned in accordance with the Helsinki Declaration and the Korean Good Clinical Practice Guidelines to protect the participants and was approved by the Medical Ethics Committee Board of Baoshan Hospital of Integrated Traditional Chinese Medicine and Western Medicine, Shanghai (201709–02). The participants will be informed of the potential benefits, risks, alternatives, and responsibilities of the study by the researchers during the consent process. They will be fully aware that they are free to withdraw from the study at any time. Any AEs (described as unfavorable or unintended signs, symptoms, or diseases occurring after treatment) related to acupuncture treatment will be observed and reported by patients and practitioners during each patient visit. In addition, all vital signs and AEs will be measured and recorded during each visit. The findings will be disseminated in peer-reviewed journals and conference presentations.

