### Safety issues

Adverse events (AEs) will be recorded using the standard operating procedures for monitoring and reporting all AEs, which refer to all the harmful and unintended reactions that occur during the acupuncture treatment. The symptoms, date of occurrence, disappearance, causality, and severity of the AEs will be recorded. The putative AEs of acupuncture include the following: local bleeding or hematoma; more than slight sharp pain; aggravation of symptoms; syncope; nausea; headache; peripheral nerve injury; and infection. Participants will be informed of the potential AEs in advance.

During the study period, all researchers will ensure patient safety. When SAEs occur, the researchers will immediately halt the study and promptly provide appropriate management. The PI will also report the AEs to the IRB and halt the study partially or completely until further notice. Then, the IRB will determine whether the clinical study can be continued. The trial will be stopped if the IRB speculates unacceptable risks of SAEs. The hospital provides insurance coverage for harm associated with the interventions during this trial as necessary.

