#### Statistical analysis

In this study, rather than the investigator, professionals will analyze the data using intention-to-treat and per-protocol approaches. The demographic and clinical characteristics of the participants (such as sex and age) will be processed based on descriptive analyses. The ECWM values and ESA scores will be compared as a baseline measurement. The quantitative data will be presented as average, standard deviation, median value, and range, while the qualitative data will be presented as the frequency and percentage.

For the primary and secondary outcome measurements, one-way ANOVA test will be applied to identify the differences between the of ECWM values and ESA scores among the groups. In case of abnormally distributed data, Kruskal–Wallis H test will be performed.

All AEs reported during the study will be included in the clinical report; then, the prevalence of AEs will be calculated. The percentage of participants with AEs in each group will be calculated and compared using the chi-squared or Fisher’s exact test. Statistical analyses will be performed using IBM SPSS Windows version 19.0 (IBM Co., Armonk, NY, USA). The tests were two-sided; a *P* value < 0.05 will be considered statistically significant.

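### Adverse events are defined with conflicting timing and scope, and the between-arm comparison does not say which definition or collection window applies

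*Protocol article*

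**What the plan says.** Four parts of the protocol article bear on AEs.

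- **Safety issues** gives one definition: AEs "which refer to all the harmful and unintended reactions that occur during the acupuncture treatment". It adds: "The symptoms, date of occurrence, disappearance, causality, and severity of the AEs will be recorded".
- **Ethics and dissemination** gives another, in parentheses, and continues directly after it: "unfavorable or unintended signs, symptoms, or diseases occurring after treatment) related to acupuncture treatment". Patients and practitioners observe and report these at each visit. The next sentence is wider: "In addition, all vital signs and AEs will be measured and recorded during each visit".
- **Statistical analysis** sets the reporting and the test: "All AEs reported during the study will be included in the clinical report; then, the prevalence of AEs will be calculated", and then "The percentage of participants with AEs in each group will be calculated and compared using the chi-squared or Fisher’s exact test".
- **Follow-up** places a contact, by clinic visit or telephone, three months after the first session. Its stated content is how hypophasis has progressed and whether it has recurred. AEs are not mentioned.

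Two facts from Study setting also matter. Treatment is planned for one month, and it stops early in a participant who recovers completely.

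**The concern.** Each of the two descriptions is written as a statement of what an AE is, and they do not describe the same set of events. One is tied to the treatment and to reactions. The other is tied to the time after treatment and covers any unfavorable sign, symptom or disease. The planned comparison of AE percentages uses the term without choosing between them.

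At stake is the safety statement. The abstract presents the trial as the first to assess the safety of Bi'nao, and the AE comparison is the only formal test that supports this. Safety issues itself lists infection, peripheral nerve injury and aggravation of symptoms as possible AEs. These need not show while needles are in place, or even before the last session. If the window follows the treatment, such events may go uncounted, and the time during which each participant is observed depends on how quickly that participant recovers.

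**Working it through.** **Is there a figure to reproduce?** No. The document states no AE rate, and its sample size calculation concerns the primary outcome only. The check is therefore mainly a comparison of texts.

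**The two definitions side by side**

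| | Safety issues | Ethics and dissemination |
|---|---|---|
| Timing | during the acupuncture treatment | after treatment |
| Scope | harmful and unintended reactions | unfavorable or unintended signs, symptoms or diseases |
| Relatedness | causality recorded for each AE | related AEs reported by patients and practitioners; next sentence records all AEs |

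**Step 1: two readings of the timing in Safety issues.** If it means the needling session, an event between sessions is outside that definition but inside the other. If it means the whole course, which is how the article uses the word treatment elsewhere, events between sessions are covered by both. Under both readings, an event that begins after the last session is outside the Safety issues definition and inside the Ethics and dissemination one.

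**Step 2: how long is the unassigned period?** Treatment lasts one month and the follow-up is three months after the first session: 3 − 1 = 2 months for a participant who completes the course. No visit is described in that period, and the contact that ends it is not said to ask about AEs.

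**Step 3: is the window the same in every arm?** Not necessarily. Because therapy stops on complete recovery, a treatment-bound window closes earlier for those who recover early. As an assumed example, a participant who recovers after two of the four weeks is observed for half as long as one who completes the course. If recovery is faster in one arm, that arm has less AE observation time.

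**Step 4: could the definition change the comparison?** The following counts are assumed, with 33 participants per group, and only show sensitivity.

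| Assumed events counted (A/B/C) | Percent | Three-group chi-squared p |
|---|---|---|
| In-session reactions only: 3/2/2 | 9.1 / 6.1 / 6.1 | 0.86 |
| Related events after treatment: 6/3/2 | 18.2 / 9.1 / 6.1 | 0.26 |
| All AEs: 9/5/2 | 27.3 / 15.2 / 6.1 | 0.063 |

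For two arms, two-sided Fisher exact tests give p = 0.43 for 5/33 versus 2/33 and p = 0.044 for 9/33 versus 2/33. Changing one count removes the second result: 8/33 versus 2/33 gives p = 0.08, and 9/33 versus 3/33 gives p = 0.11. The percentages move with the definition, but the document supplies nothing from which to predict by how much.

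**The case against.** The strongest reply is that the rest of the text largely repairs the wording. Two stronger criticisms are tempting, and the documents support neither.

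- **A reader might infer that unblinded practitioners screen out events they judge unrelated.** Randomization and blinding does give the assignment to the treating doctors. In Ethics and dissemination, however, the definition is the parenthesis alone, and relatedness stands outside it. The next sentence records all AEs at each visit, Safety issues records causality as an attribute, and no section allows practitioners to exclude events. Patients, who are blinded to the type of acupuncture, report as well. The relatedness phrase is an ambiguity in one sentence.
- **A reader might infer that the comparison has no numerator.** Statistical analysis names one: participants with AEs, from all AEs reported during the study. The fault is that this numerator rests on an inconsistent definition and window.

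The reply also holds that the timing conflict shrinks on the whole-course reading, which the listed AEs favor. That is fair for events between sessions. It does not cover events after the last session or the earlier closing of the window on recovery.

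Finally, the detail may sit in the standard operating procedures that Safety issues cites, which are not shown. That would answer a complaint about missing detail. It does not answer two stated definitions that disagree.

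**Conclusion.** The point holds in a limited form. The two definitions conflict in timing and scope, and the between-arm comparison does not choose between them. On the Safety issues wording, harm arising after the last session is not an AE and the observation window depends on recovery. The contact at which later harm could be picked up is not described as asking about it.

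The size cannot be derived, because no AE rates are given. The p-values above rest on chosen counts, so they do not show that the safety conclusion would reverse. That the window differs by arm also rests on an assumption, namely that recovery speed differs between arms. The sample size and the primary analysis are not affected. This is a safety-reporting weakness that is cheap to correct, and Trial status describes recruitment as ongoing, so later events can still be collected.

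**What to change.** Reconcile Safety issues, Ethics and dissemination, and Statistical analysis so that they share:

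1. One all-cause definition: any unfavorable or unintended sign, symptom or disease, whether or not it is judged related to acupuncture.
2. One fixed calendar window for every participant, from the first session to the three-month follow-up, including those whose therapy ended early on recovery.
3. An AE question added at the existing three-month contact, in both its clinic and telephone forms.
4. Relatedness kept only as a recorded attribute and never as a condition for recording. The sentence in Ethics and dissemination should be reworded to say so.
5. The between-arm comparison stated to use this all-cause count over this window.

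The cost is protocol and case report form wording plus one question at a contact that already takes place. The downside is that more minor, unrelated events will be recorded.

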## Discussion

The present study evaluated the efficacy of acupuncture therapy on the acupoint Bi’nao for hypophasis in patients with Bell’s palsy based on the previous studies and our clinical experience. When planning a manual acupuncture study, the duration of treatment, treatment points, and frequency of stimulation should be considered as these can affect the outcomes of acupuncture. However, in a RCT, only one variable could be tested. Thus, we established this regimented acupuncture protocol that has been discussed and optimized at the Baoshan Hospital of Integrated Traditional Chinese Medicine and Western Medicine, Shanghai.

In addition, the function of “De qi” will be considered in the trial; it is based on subjective reporting of the patient (soreness, numbness, fullness, radiating sensation) and is regarded as a sign of efficacy according to TCM. A majority of the contemporary acupuncturists still seek “De qi,” rendering it as fundamental to efficacy. The placebo effect produced by sham acupuncture was considered to influence the disease lightly, although needle pricking might induce non-specific physiological reactions. The sensation of “De qi” can be accurately described by sense felt by either the practitioner or patient, and reliable scales such as the Massachusetts General Hospital Acupuncture Sensation Scale (MASS) have already been applied in clinics measuring the intensity of “De qi” sensation [24–26].

The assessment of hypophasis is rather challenging due to the lack of a widely recognized method or scale. The House-Brackmann scale and Sunnybrook Grading System are suitable for the overall assessment of Bell’s palsy, but are not applicable to individual symptoms such as hypophasis. Thus, we created the ECWM and ESA to evaluate eyelid movement according to some neurological function classification. Although this was an innovative approach, it was also a limitation of this study.

The results showed that the acupuncture treatment on the acu-point Bi’nao is a safe and effective method for improving hypophasis. Furthermore, the study provided evidence to support the application of acupuncture therapy in the management of Bell’s palsy and its sequelae in the future.

### Trial status

This trial began in September 2017 after IRB approval. Trial completion is expected by the end of June 2020. Recruitment is currently ongoing.

## Abbreviations

AE: Adverse event
CONSORT: Consolidated Standards of Reporting Trials
CRC: Clinical research coordinator
ECWM: Eye Crack Width Measurement
ESA: Eyelid Strength Assessment
IRB: Institutional review board
SOP: Standard operating procedure
SPIRIT: Standard Protocol Items Recommendations for Interventional Trials
STRICTA: Standard for Reporting Interventions in Clinical Trials for Acupuncture
TCM: Traditional Chinese medicine
